## Abstract

**Background:**

Several feasibility studies show promising results of telehealthcare on health outcomes and health-related quality of life for patients suffering from chronic obstructive pulmonary disease, and some of these studies show that telehealthcare may even lower healthcare costs. However, the only large-scale trial we have so far - the Whole System Demonstrator Project in England - has raised doubts about these results since it conclude that telehealthcare as a supplement to usual care is not likely to be cost-effective compared with usual care alone.

**Methods/Design:**

The present study is known as ‘TeleCare North’ in Denmark. It seeks to address these doubts by implementing a large-scale, pragmatic, cluster-randomized trial with nested economic evaluation. The purpose of the study is to assess the effectiveness and the cost-effectiveness of a telehealth solution for patients suffering from chronic obstructive pulmonary disease compared to usual practice. General practitioners will be responsible for recruiting eligible participants (1,200 participants are expected) for the trial in the geographical area of the North Denmark Region. Twenty-six municipality districts in the region define the randomization clusters. The primary outcomes are changes in health-related quality of life, and the incremental cost-effectiveness ratio measured from baseline to follow-up at 12 months. Secondary outcomes are changes in mortality and physiological indicators (diastolic and systolic blood pressure, pulse, oxygen saturation, and weight).

**Discussion:**

There has been a call for large-scale clinical trials with rigorous cost-effectiveness assessments in telehealthcare research. This study is meant to improve the international evidence base for the effectiveness and cost-effectiveness of telehealthcare to patients suffering from chronic obstructive pulmonary disease by implementing a large-scale pragmatic cluster-randomized clinical trial.

**Trial registration:**

Clinicaltrials.gov, http://NCT01984840, November 14, 2013.

## Background

The World Health Organization (WHO) has estimated that globally more than 64 million people have chronic obstructive pulmonary disease (COPD) and that more than 3 million people died of COPD in 2005, which was 5% of total deaths that year [1]. The prevalence of COPD in Denmark is among the highest in the world [2]. It is estimated that COPD affects 430,000 Danish citizens, that is, 7% of the entire population and 14% of citizens older than 35 years [3]. It is also estimated that around 5,000 citizens die due to COPD each year, which makes COPD the fourth largest cause of death in the country [4].

COPD is one of eight diseases that have been given priority by the Danish Health and Medicines Authority since 2002. Around 10 percent of the total annual Danish healthcare budget for citizens over 45 years is related to care and treatment of COPD; the costs are in excess of £300 million per year [4].

Recent systematic reviews show promising results of telehealthcare on health outcomes and health-related quality of life in COPD patients [5-7], and some feasibility studies indicate that the use of telehealthcare may lower the costs of such care [8-13]. These studies have fuelled clinical and political interest in telehealthcare as a way of improving COPD patient outcomes while cutting costs. However, there has been a call for large-scale clinical trials with rigorous cost-effectiveness assessments in telehealthcare research [14], and concerns about the quality of the current evidence have been raised [7,14]. The studies have a limited number of participants (typically fewer than 200) and have not been conducted in routine clinical practice. In addition, the evidence base on costs could be improved, and the studies usually do not draw conclusions on the cost-effectiveness of telehealthcare. This hampers a comparison of the expected health benefits and costs from telehealthcare with those that may be obtained from the use of other health technologies. Finally, in the recently published ‘Whole System Demonstrator Project’ in the United Kingdom, the largest clinical study published so far, doubts were raised about the effect of telehealthcare. Thus, the UK study concludes that telehealthcare is not a cost-effective addition to usual care [15]. However, a debate on the validity of the conclusions in the Whole System Demonstrator Project study is ongoing in Denmark for at least two reasons. First, the conclusion of the UK study might be biased since trial recruiters had foreknowledge of the allocation groups in many cases [16]. Second, its transferability to a Danish context is an issue since the trial did not consider all community and healthcare resources [15]. Addressing the latter issue is particularly important since general practitioners and municipalities are responsible for the care and monitoring of COPD patients in Denmark.

Healthcare decision makers in Denmark have therefore agreed to improve the evidence base on the effectiveness and cost-effectiveness of telehealthcare for COPD patients. As part of ‘The National Danish Action Plan for Dissemination of Telemedicine’, a full-scale, pragmatic, cluster randomized trial with a nested economic evaluation has therefore been designed for the geographical area of the North Denmark Region. This Region is one of five regions in Denmark with responsibility for healthcare for 580,000 citizens. The results of the trial will inform a political and clinical decision to implement a particular telehealthcare solution as a national standard for COPD treatment and care in Denmark [17].

The objectives of this trial are divided into two themes. The first theme has the objective to evaluate whether a particular telehealth solution that is serving as an adjunct to usual care significantly increases the health-related quality of life of patients suffering from COPD compared with usual practice. The second theme has the objective to evaluate the cost-effectiveness of this telehealth solution.

## Methods/Design

### Study design

This trial, which is known as ‘TeleCare North’ in Denmark, will be implemented in 2014and 2015. It is a full-scale, pragmatic, two-level, cluster randomized trial with 12 months of follow-up in the entire region of North Denmark Region. The municipality districts in the region define the clusters. Each municipality has between one and five districts depending on its size.

The two-level, cluster randomized, controlled study where municipality districts define the clusters was chosen for the following reasons: First, using general practitioners as both participant recruiters and randomization units could lead to selection bias concerns. To eliminate these kinds of randomization concerns, it was decided to randomize clusters at a different organizational level. Second, municipalities are organized into one or more self-contained community care districts defined by geography and personnel who provide services to COPD patients therefore usually do not overlap between districts. The cluster-randomization could therefore eliminate the risk of contamination between practices in the two alternative arms. Third, the municipality is a natural level of randomization since the responsibility for caring for and monitoring of COPD patients via the telehealth solution would eventually fall on the municipalities. Fourth, all municipalities wished to be in the telehealthcare group to provide such services at least to some of their citizens. It was therefore pragmatically decided to make these services available on a district basis within the municipalities.

### Participants

Ten out of 11 municipalities in the North Denmark Region are included in the study. One municipality (‘Læsø’) was excluded for practical reasons. The municipality has only one district and is constituted by a small island off the east coast of Jutland; it has 1,840 inhabitants (0.3% of the total inhabitants in the North Denmark Region) and one general practitioner. Matching this municipality district with other municipalities on the mainland would be difficult and questionable.

The inclusion criteria for individual participants are equivalent to those listed in the guidelines from ‘The Global Initiative for Chronic Obstructive Lung Disease (GOLD)’ [18] and other telehealthcare projects. The inclusion criteria are summarized as ‘all COPD patients that may benefit from telehealthcare’. Participants are eligible for inclusion if they have been diagnosed with COPD by spirometry and are receiving treatment as indicated in the GOLD guidelines. In addition, a general practitioner must indicate COPD as the patient’s primary disease. Patients must have a fixed residence and be listed with a general practitioner in the North Denmark Region. At least one of the following criteria should also be met: The Modified Medical Research Council scale (mMRC) ≥2 or mMRC ≥3 and COPD Assessment Test (CAT) ≥10, and have had at least two exacerbations within the past 12 months. Patients must have a phone connection and be able to speak Danish or they must be living with a Danish-speaking relative. The relative must be able to support the patient in using telehealthcare in situations where the patient cannot use the monitoring device or has problems with language or communication. Patients are excluded if they have no phone line or GSM coverage, are unable to understand Danish sufficiently to complete the study questionnaires or have a cognitive impairment.

### Recruitment

To ensure that the ten municipalities are represented in both treatment arms, the 26 municipality districts (the clusters) are paired 1:1 within the municipalities. Paired districts are paired in terms of population size, estimated proportion of citizens suffering from COPD over 40 years of age, and unemployment rate. In the municipalities of ‘Aalborg’ and ‘Frederikshavn’, the number of districts is uneven; we therefore matched the district in ‘Aalborg’ with a district in ‘Frederikshavn’ that has approximately the same population size. The COPD rate is a guess made by the trial administration office based on the number of citizens in each municipality district redeeming oral prednisolone prescriptions.

All general practitioners in these municipality districts (n = 344) are contacted by the trial administration office and invited to draw up a list of eligible COPD patients from their practice based on the inclusion criteria of the trial. At the same time, five to eight so-called ‘Telekit packages’ will be sent from the trial administration office to each practice. The ‘Telekit packages’ contain a brochure describing the trial in detail, a detailed description of patient eligibility criteria, an informed consent form for the patients to sign, a form to be filled in with baseline physical measurements, a patient-questionnaire, and two postage-paid envelopes. Voluntary information meetings targeting general practitioners are arranged at four different dates by the trial administration office. The objective, the organization of the trial, and the expectations of the participating general practitioners will be explained at these meetings.

Eligible patients are enrolled by the general practitioners. All general practitioners (supported by their local union) have agreed in advance of the trial to make individual appointments with each eligible patient listed with their practice. Before the appointment, the general practitioner posts a written folder to the patients informing them about the study and their legal rights. The appointment lasts approximately 30 minutes per patient. At the appointment, the general practitioner repeats information about the trial, hands out the same information folder that was sent to the patient before the appointment, takes baseline physical measurements (spirometry, mMRC and CAT scores, weight, pulse and blood pressure), and written informed consent is obtained if the patient accepts trial participation. If the general practitioner has obtained physical measurements less than 30 days before the appointment, these data can be used as baseline physical measurements instead.

The general practitioner sends the signed informed consent forms together with the list of eligible patients and the filled in forms with baseline physical measurements to the trial administration office using the first pre-stamped envelope. The general practitioner also distributes the patient-questionnaire which includes questions about the patients’ baseline health-related quality of life (EQ5D and SF-36) and demographic characteristics (age, gender, education, comorbidities, smoking status, marital and job status). The patient-questionnaire is filled out in the comfort of the patients’ own homes no later than two weeks after their visit to the general practitioner and must be sent to the trial administration office using the second pre-stamped envelope. The trial administration’s telephone number is printed on the questionnaires and patients are invited to contact the office if they need help to answer the questionnaire. Both envelopes are returned to the office before randomization.

Finally, the general practitioners electronically refer patients eligible for inclusion into the trial to the residing municipality where threshold values for body mass index, blood pressure, and blood oxygen saturation are established. These threshold values are individually determined for each patient and will be used in the monitoring of the patients by the municipalities’ community healthcare personnel.

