### Randomization

Municipality districts are randomized so that all patients living within the same municipality district receive either telehealthcare in addition to usual care or just usual care. The randomization will not be undertaken until after all general practitioners have sent their lists of patients eligible for inclusion from their practice, and after all patients have given written consent to participation and completed baseline physical measurements and questionnaires. There will be 13 individual randomization ‘draws’ from the 26 matched municipality districts. The randomization will be done by the sealed envelope method by a person not affiliated with the trial. The randomization event will be videotaped.

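### The 13 within-pair draws make no use of district enrolment and baseline scores already on file, and baseline adjustment is left optional, so avoidable chance imbalance is accepted

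*Protocol article*

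**What the plan says.** Under Recruitment, the protocol article states that "the 26 municipality districts (the clusters) are paired 1:1 within the municipalities". The matching variables follow: "Paired districts are paired in terms of population size, estimated proportion of citizens suffering from COPD over 40 years of age, and unemployment rate". On the COPD figure it says: "The COPD rate is a guess made by the trial administration office", and that this is "based on the number of citizens in each municipality district redeeming oral prednisolone prescriptions". Two municipalities have an odd number of districts, and for the pair that crosses their border the text reads: "we therefore matched the district in ‘Aalborg’ with a district in ‘Frederikshavn’ that has approximately the same population size". No other variable is named for that pair.

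Under Participants, eligibility rests on a spirometry diagnosis, on mMRC, CAT and exacerbation criteria, and on the rule that "a general practitioner must indicate COPD as the patient’s primary disease".

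Under Randomization, the draw takes place only "after all patients have given written consent to participation and completed baseline physical measurements and questionnaires". The Recruitment section confirms that both return envelopes, one of them holding the SF-36 and EQ5D questionnaire, are back at the office by then. Allocation is by 13 individual draws, one per pair, with sealed envelopes and a person from outside the trial.

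Under Statistical methods, adjustment for patient or cluster baseline characteristics is conditional on being appropriate. The examples are age, gender, comorbidities, education, marital status and the proportion of COPD patients. Baseline SF-36 and EQ5D are not among them. QALYs are the area under a straight line from baseline utility to 12-month utility.

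**The concern.** A count of people redeeming prednisolone does not measure spirometry-confirmed COPD, COPD as primary disease, symptom scores or consent. Enrolment also depends on how many patients each practice lists and how many of them agree. The pairs may therefore be only loosely alike in the two things that matter for comparing the arms: how many patients each district contributes and how those patients score at baseline.

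In most cluster trials nothing better is known before allocation. Here, because the draw waits until recruitment is complete, both quantities can be known for every district beforehand. With 26 unequal clusters, 13 separate draws can leave the arms visibly different in size and in baseline PCS and utility. Those two scores feed the two primary outcomes, and the analysis text does not commit to adjusting for either.

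**Working it through.** **1. The plan's sample size.** Inputs from Sample size: difference 5, SD 10, cluster size 50, CV 0.5, ICC 0.05, power 80%, two-sided 0.05.

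- Per arm without clustering: 2 × (10 × (1.960 + 0.842)/5)² = 62.8.
- Design effect: 1 + ((1 + 0.5²) × 50 − 1) × 0.05 = 4.075.
- 62.8 × 4.075 = 255.9 per arm; 255.9/50 = 5.12, rounded up to 6 clusters. Adding one for a small number of clusters (my inference) gives 7, and 7 × 50 = 350, as stated.
- 10% loss: 700/0.9 = 778, in line with the stated total of around 800.

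No credit is taken for matching. A 13-pair analysis (12 degrees of freedom) with uninformative pairing has about 96% power at 700 patients and 98% at 1,200. Weak matching therefore does not threaten power.

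**2. Chance imbalance in baseline PCS.** 1,200/26 = 46 per district. Variance splits into 5 between districts (0.05 × 100) and 95 within.

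- Equal sizes, uninformative pairing: √[(2/13) × (5 + 95/46)] = 1.04 points.
- CV 0.5: design effect 1 + (1.25 × 46.15 − 1) × 0.05 = 3.83; √[(2/13) × 100 × 3.83/46.15] = 1.13 points.
- Simulation over all 2¹³ = 8,192 allocations: root-mean-square (RMS) difference about 1.1 points if pairing captures none of the between-district variance, 0.9 if it captures half (assumed range). The difference exceeds 2 points in about 7% and 3% of draws.

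**3. Chance imbalance in arm size.** District SD is 0.5 × 46.15 = 23.1.

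- Uninformative pairing: √(13 × 2 × 23.1²) ≈ 118 patients between arms, or 59 either side of 600.
- Within-pair correlation 0.5: 118 × √0.5 ≈ 83; simulation gives about 84.
- A 541:659 split costs about 1% in efficiency: 4 × 541 × 659/1,200² = 0.99.

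**4. Passage into the QALY difference.** Per patient, QALY = (U₀ + U₁₂)/2 over one year. A baseline gap d between arms therefore adds d/2 directly, before any carry-over to 12 months. The documents give no EQ5D SD. With an assumed SD of 0.15 to 0.25 and the same ICC, the typical gap is 0.112 SD (1.12/10), or 0.017 to 0.028, which adds about 0.008 to 0.014 QALY.

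**5. What a constrained draw achieves.** Keep the best-balanced 10% of the 8,192 allocations, ranked by the sum of squared standardized differences. The last two rows assume a PCS–EQ5D correlation of 0 to 0.7.

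| Balanced on | Pairing captures | RMS PCS difference | RMS size difference |
|---|---|---|---|
| size, PCS | none | 0.28 | 29 |
| size, PCS | half | 0.23 | 21 |
| size, PCS, EQ5D | none | 0.37–0.41 | 40–43 |
| size, PCS, EQ5D | half | 0.30–0.34 | 29–31 |

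Across repeated runs the three-variable constraint leaves about 0.29 to 0.42 points and 28 to 45 patients.

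**6. How many pairs are forced.** Ten municipalities hold 26 districts, at most five each, and only two have an odd number. If those two hold 3 or 5 each, 20, 18 or 16 districts remain for eight municipalities with 2 or 4 each, so six to eight of them have exactly two. If both hold one, 24 remain and four have exactly two. In those municipalities the pair is fixed whatever the matching variables say.

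**The case against.** Pair-matched randomization by an outside person after enrolment closes is valid and well concealed. Chance imbalance is already reflected in the standard error, and the sample size claims nothing from matching. The first primary outcome is a change from baseline, so a baseline PCS gap does not pass straight into the effect, and adjustment is foreseen. The loss from unequal arms is about 1%, and a PCS gap above half the planned 5 points arises in roughly 2% of draws or fewer. Preferring a constrained draw to simple pairs can be called a matter of taste. All of this stands as to validity and power.

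It does not dispose of the point. A change score does not by itself remove the effect of a baseline imbalance. The adjustment is conditional and does not name the baseline scores. The QALY calculation has no correction for baseline utility.

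Several stronger readings are tempting, and the documents do not support them:

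- *The matching figure fails to describe eligible patients.* The protocol shows that it is indirect. It gives no data on how well it tracks them, and exacerbations are part of eligibility.
- *Poor matching spoils the pairing throughout.* Many pairs are forced by municipality.
- *The Aalborg–Frederikshavn pair ignored the other variables.* Only population size is named; the text does not say that the rest were disregarded.
- *The imbalance can be removed at no cost.* It can be reduced, and paper questionnaires for about 1,200 patients must first be entered and scored.

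**Conclusion.** The point holds as a worthwhile improvement, not as an error that endangers the trial. The documents establish that the pairing rests on indirect area-level figures, that better data are in hand before allocation, that the draws do not use them, and that adjustment for the baseline scores is not fixed. The consequence is avoidable chance imbalance of about 0.9 to 1.1 PCS points (RMS) against a planned difference of 5, and 84 to 120 patients between arms. The QALY result is the more exposed, since half of any baseline utility gap enters it directly. These sizes rest on the protocol's SD, ICC, CV and expected enrolment, on pairing assumed to capture between none and half of the between-district variance, and, for utility, on an assumed SD. A reader might infer bias or an underpowered trial; neither follows.

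**What to change.** Recruitment was still open when the article was written and the draw comes afterwards, so both steps are feasible. The first stands on its own if the second is not adopted.

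1. Make adjustment for individual baseline PCS a fixed part of the theme 1 primary analysis, and adjustment for individual baseline EQ5D utility a fixed part of the QALY difference, in place of the conditional wording. The data are collected anyway, so this costs nothing.

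2. Keep the existing pairs, but replace the 13 separate draws with one. Before any data are examined, fix the imbalance score (number enrolled, mean baseline PCS and mean baseline EQ5D per district), the fraction retained (for example the best 10%, about 819 of 8,192) and the handling of missing items. Number the retained allocations and let the outside person draw one at the filmed event. An allocation and its mirror image have the same squared-difference score, so each district keeps an even chance of either arm if ties at the cut-off are retained together. Include the constraining variables in the model.

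The second step needs a little programming, and all baseline questionnaires must be entered and scored before the draw, which could delay it. The 13 envelopes also become one numbered list, which is slightly harder to explain to the municipalities.

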#### Intervention

The telehealth solution is a tablet (Samsung Galaxy Tab2 (10.1)) that contains information on handling COPD in general and software that automatically instructs the patient in handling COPD during exacerbations. The device can also collect and wirelessly transmit relevant disease-specific data indicative of the patient’s current state of health: blood pressure, pulse, blood oxygen saturation, and weight. This is made possible via an attached Fingertip Pulse Oximeter (Nonin, Onyx II% SpO2, A & D Medical, Tokyo, Japan), a Digital Blood Pressure Monitor (Model UA-767, plus BT-C, Nonin Medical, Minnesota, USA), and a scale (Precision Health Scale, UC-321PBT-C, A & D Medical, Tokyo, Japan). The software was developed by Silverbullit, Aarhus, Denmark (http://opentele.silverbullet.dk). The tablet can be activated and sound an alarm when it is time for taking measurements again. Patients and their relatives can access the data via a web portal (http://www.sundhed.dk).

At the cluster-level, around 100 municipality healthcare personnel (mostly community care nurses) will be responsible for patient care and monitoring in the intervention group. They will be trained by members of the trial administration office. The training consists of two full-day workshop sessions: Session 1 focuses on the technical aspects of the tablet (how to use it) and the physical measurements (how to perform the measurements using the tablet and how to monitor threshold values). Session 2 focuses on general disease awareness and communication with patients.

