### Outcomes

The primary outcome for theme 1 (effectiveness) is the change in health-related quality of life (SF-36) at the individual level from baseline to follow-up at 12 months. This study hypothesizes that adding telehealthcare to usual care will lead to a significantly higher health-related quality of life for the included participants.

Secondary outcomes for theme 1 are changes in mortality and physiological parameters (diastolic blood pressure, systolic blood pressure, pulse, oxygen saturation, and weight) from baseline to the follow-up at 12 months. The clinical impact of telehealthcare is assessed as being beneficial if there is no changes in mortality and if pulse and blood pressure are lowered and oxygen saturation is raised.

The primary outcome for theme 2 is the incremental cost-effectiveness ratio (ICER) measured as the cost per quality adjusted life years (QALY) gained from baseline to follow-up at 12 months. It is expected that telehealthcare will increase the patients’ QALY compared with usual practice, since no difference in mortality and a higher health-related quality of life are expected. Furthermore, it is hoped that telehealthcare will reduce the number of admissions and readmissions to hospitals as well as the number of outpatient visits by 30%, which will reduce hospital costs [13,19]. However, these savings could be offset by other costs such as more visits to general practitioners, community care, medicine consumption or the cost of implementing telehealthcare.

Outcomes will be measured at both the individual level and at cluster level.

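### Change in oxygen saturation is a secondary outcome, but the listed baseline measurements omit saturation, so neither arm has a stated baseline value

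*Protocol article*

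**What the plan says.** **The outcome.** For theme 1, the Outcomes section of the protocol article names as secondary outcomes, besides mortality, the changes in "physiological parameters (diastolic blood pressure, systolic blood pressure, pulse, oxygen saturation, and weight) from baseline to the follow-up at 12 months". Saturation is also named in the Abstract. Outcomes then says that the clinical impact will be judged beneficial when mortality does not change and "if pulse and blood pressure are lowered and oxygen saturation is raised". Statistical methods plans a between-arm comparison of the baseline-to-12-month differences in physical measurements.

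**The baseline.** According to Recruitment, each practice receives "a form to be filled in with baseline physical measurements". At the enrolment visit the general practitioner "takes baseline physical measurements (spirometry, mMRC and CAT scores, weight, pulse and blood pressure". The completed form goes to the trial office. Under Randomization, the draw waits until "after all patients have given written consent to participation and completed baseline physical measurements and questionnaires".

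**Other mentions of saturation.** Recruitment ends with an electronic referral of eligible patients to their municipality, "where threshold values for body mass index, blood pressure, and blood oxygen saturation are established"; these limits serve later monitoring. The Intervention section describes a tablet that collects and transmits saturation: "This is made possible via an attached Fingertip Pulse Oximeter". Intervention patients are contacted about receiving the tablet within 10 days after randomization. Under Usual practice, control patients simply continue their existing care.

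**The concern.** An outcome defined as change needs a value at both ends. The article says which measurements make up the baseline, and that list leaves out one of the quantities whose change is to be analysed. If sites follow the list, the trial reaches randomization without the value that the outcome definition and the planned analysis require. A pre-randomization reading cannot be recovered after that.

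What is at stake is one named secondary outcome and one element of the sentence on clinical benefit. Trial status says that recruitment is ongoing, and randomization waits for all baseline data, so the gap can still be closed for patients not yet enrolled.

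**Working it through.** The plan gives no figure to reproduce here. The check sets the outcome list against the baseline list.

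| Physiological outcome (Outcomes) | In the stated baseline set (Recruitment)? |
|---|---|
| Diastolic blood pressure | yes, as blood pressure |
| Systolic blood pressure | yes, as blood pressure |
| Pulse | yes |
| Weight | yes |
| Oxygen saturation | no |

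Four of the five outcomes have a stated baseline; saturation does not.

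Next, could a baseline come from elsewhere in the article?

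1. *Packages sent to practices.* The listed contents are paper items and envelopes. The measurement form is among them, but its fields are not given and no measuring device is listed.
2. *Threshold setting.* This step covers eligible patients without regard to arm and is described as part of recruitment. It produces an individual limit for monitoring. The article does not say that a saturation reading is taken, stored or sent to the trial office.
3. *The tablet's oximeter.* It belongs to the intervention and is handed over after randomization. The Randomization section requires baseline measurements to be complete before the draw, so a tablet reading falls outside the protocol's own baseline.
4. *Usual care.* No saturation reading is described for control patients.

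None of the four supplies a stated pre-randomization value, and this is true of both arms.

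Finally, what would be lost by analysing the 12-month value instead? Let σ² be the variance of saturation, assumed equal at both times, and ρ the correlation between baseline and 12 months. Leaving clustering aside, the per-patient variances are:

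- 12-month value alone: σ²
- change from baseline: σ² + σ² − 2ρσ² = 2σ²(1 − ρ)
- 12-month value adjusted for baseline: σ²(1 − ρ²)

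Under randomization all three target the same between-arm difference. The adjusted analysis is never worse than the other two, because 1 − ρ² ≤ 1 and 1 − ρ² = (1 − ρ)(1 + ρ) ≤ 2(1 − ρ). Change is more precise than the unadjusted 12-month value only if 2(1 − ρ) < 1, that is, ρ > 0.5. The article gives neither ρ nor a standard deviation for saturation, so the loss cannot be put as a number. It is a loss of precision and not a bias.

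**The case against.** The best counter-argument is that a bracketed list in a journal article is not the case report form. The form's fields are not shown, and the full protocol may well include saturation. The list may also be incomplete in another respect: thresholds are set for body mass index, yet height is not listed. A reading could also be taken when the saturation threshold is set. All of this stands, and it limits the finding to what the article states. It does not remove the mismatch. The article is not silent about baseline; it gives a specific list, with no wording to mark it as examples, and that list disagrees with its own outcome list.

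The counter-argument does rule out several stronger readings that a reader might infer:

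- *That the change cannot be calculated.* The article shows only that no baseline is stated. It does not show that none is collected.
- *That the gap is confined to controls, about half of the 1,200 expected participants.* Neither arm has a stated pre-randomization value. The half also assumes an even split, whereas districts are randomized and no expected arm sizes are given.
- *That the comparison will be biased because first tablet readings will serve as baseline in one arm.* No section proposes this, and the timing rule under Randomization already excludes it.
- *That a formal decision rule fails.* The sentence on clinical benefit has no thresholds or test attached and does not govern the primary outcomes.

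It is also true that a between-arm comparison at 12 months remains valid without a baseline. That is a sound fallback, but it is not what Outcomes and Statistical methods specify, so the wording would have to change.

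**Conclusion.** The point holds as a conflict between two stated parts of the article. Outcomes and Statistical methods call for change in saturation from baseline, while the baseline set in Recruitment does not contain saturation. As written, the value is unstated for every participant in both arms. The extent is one of five physiological outcomes and one element of the clinical-benefit sentence. The primary outcomes (SF-36 and the incremental cost-effectiveness ratio) and the other four physiological outcomes are untouched.

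The conclusion rests on taking the Recruitment list as complete. If the form already records saturation, the problem shrinks to a text correction. The article also does not describe how 12-month physical measurements are obtained; an article may leave that to the full protocol, and it is not counted here.

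**What to change.** Before randomization, check the baseline form.

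- **If it already records saturation,** correct the list in Recruitment.
- **If it does not,** add saturation to the pre-randomization baseline set and to the form for all patients still to be enrolled. The existing allowance for measurements taken less than 30 days before the visit can apply to it as well. For patients already enrolled, use a pre-randomization reading if one was recorded, for example when thresholds were set.
- **If a baseline cannot be obtained for everyone,** redefine the outcome, and the saturation part of the clinical-benefit sentence, as a between-arm comparison of 12-month saturation. Measure it by the same method in both arms and adjust for pre-randomization saturation where available. Whether a baseline value is missing is settled before allocation, so it cannot depend on the arm.

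The first option costs a text correction. The second costs one brief finger reading and one form field, at a visit that already takes pulse and blood pressure. The third costs a wording change and some precision compared with an analysis adjusted for a complete baseline.
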